A few studies have assessed change in weight from the provision of genetic-based information compared to a standard intervention [15–17]. Two studies reported that genetic testing was superior to a standard intervention for changes in weight or BMI [15, 17], and one study showed that adherence to a genetic-based diet was correlated with greater weight loss, whereas adherence to a standard diet was not [16].

There have been considerable scientific advancements in knowledge pertaining to nutrition and physical activity recommendations, which can be personalized based on an individual’s genetic variation. Nutrigenomics is a science that explores the interaction between nutrition, genetics, and health outcomes [18]. The science exploring how nutrition and physical activity, alongside other lifestyle components, can impact health outcomes can be referred to as *lifestyle genomics* [11]. Single nucleotide polymorphisms (SNPs) located within the genes FTO, MC4R, TCF7L2, UCP1, APOA2, and PPARg2 can impact physical activity and dietary approaches to weight management and/or nutritional habits [19–27]. Furthermore, SNPs located within the genes ACTN3, NFIA-AS2, ADRB3, NRF2 and GSTP1 have been shown to impact genetic predisposition to excel in either endurance or strength-based activities [28–32]. These genetic variants were used in the genetic test provided in the present study as they are currently offered through commercial genetic testing [33], thus optimizing the pragmatic nature of this trial.

While genetics certainly plays a role in obesity, there are multiple factors contributing to the current obesity epidemic, including diminished energy expenditure, increased energy intake, rising food costs, the built environment, socioeconomic status, and other social determinants of health [34–39]. Several of these factors can be modified such as energy intake and energy expenditure.

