## Methods/design

### Objectives

The primary objective of this study is to determine if the provision of genetic-based lifestyle advice reduces body fat percentage to a greater extent than the provision of population-based lifestyle advice. Secondary objectives include determining whether the provision of genetic-based lifestyle advice (a) helps to motivate healthful changes to dietary intake and physical activity, (b) leads to greater improvements in anthropometric measures such as weight, BMI, lean mass, fat mass (kg), and water weight, and (c) influences attitudes, subjective norms, behavioural control, and intention to make lifestyle changes. The tertiary objective is to determine if there is a nutrigenomics interaction between ACE rs4343 genetic variation, sodium and water intake, and water weight.

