### Hypotheses

Compared to the provision of population-based lifestyle advice, providing DNA-based lifestyle advice will lead to significantly greater improvements in: body fat percentage, attitudes and intentions towards behaviour change, the adoption of healthier dietary and physical activity habits, as well as improved weight, and BMI. Furthermore, we hypothesize that ACE rs4343 genetic variation will lead to increased water weight when sodium intake is high.

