##### PLI group meetings (intervention group)

The modified GLB™ Program curriculum is outlined in Additional file 4. The modifications allowed participants in this group to follow their DNA-based recommendations, rather than the standard population-based guidelines. For example, if an individual possessed a genetic variant in the FTO gene whereby a moderately high protein diet can enhance weight loss [21], they were given a target for protein, and were taught how to count daily grams of protein (in addition to calories). In comparison, for the standard GLB™ program, every participant was provided with a target for total fat intake and were taught how to count daily fat grams (in addition to calories). Modified GLB™ group sessions were 1 h long. In addition to the modified GLB™ Program, participants were provided with an extra 1.5 h group session (the first session), where they were given an overview of personalized DNA-based information and recommendations for calories, protein, total fat, saturated fat, total unsaturated fat, monounsaturated fat, polyunsaturated fat, meal/snack timing, and physical activity. This information is further detailed in Additional file 3. It should be noted that the genetic intervention is rated to be high-quality based on a recently developed genetic intervention quality assessment tool [11]. The quality assessment is outlined in Additional file 5.

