#### Statistical analysis plan

We plan to use SPSS Version 23.0 to conduct all statistical analyses, and the data will be analyzed on an intention-to-treat basis. Generalized linear mixed-effects models will be used to test between group differences from baseline to each follow-up period for each outcome indicator. If significant mean differences are detected, a Tukey’s post hoc test will be used to compare differences by group. General linear regression models will be used to assess interactions between a given genotype of interest and dietary component of interest on BMI and body composition. General linear regression models will further be used to assess interactions between TPB components, study group, and anthropometric measures of weight and body composition. No interim analyses will be completed.

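### The genotype-by-diet regressions do not name study group or time point although PLI diet targets followed genotype, so on pooled follow-up data a programme effect can pass for a gene-diet interaction

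*Protocol article*

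**What the plan says.** - **Model.** The Statistical analysis plan section says that general linear regressions will "assess interactions between a given genotype of interest and dietary component of interest on BMI and body composition". Study group, analysis population and time point do not appear in that sentence. The next sentence, on the Theory of Planned Behaviour (TPB), does name the arm. Those models will "assess interactions between TPB components, study group, and anthropometric measures of weight and body composition".
- **How diet was set in PLI.** The section on PLI group meetings gives the FTO example. For carriers of the relevant variant, "they were given a target for protein, and were taught how to count daily grams of protein".
- **How diet was set in the standard programme.** The same section says that there "every participant was provided with a target for total fat intake".
- **What is fixed in advance.** The tertiary objective concerns a "nutrigenomics interaction between ACE rs4343 genetic variation, sodium and water intake, and water weight". The Hypotheses section gives its direction: "ACE rs4343 genetic variation will lead to increased water weight when sodium intake is high".
- **What is left open.** The regression sentence speaks only of a genotype and a dietary component of interest. It also adds BMI, which is not part of the tertiary objective. The Background says that variants in "FTO, MC4R, TCF7L2, UCP1, APOA2, and PPARg2 can impact physical activity and dietary approaches to weight management".

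**The concern.** Intake at follow-up is measured after allocation and is shaped by it. In PLI, carriers of a diet-related variant were steered towards a particular intake. Carriers in the standard arm were not. Among carriers, then, high intake of the advised nutrient partly marks membership of PLI. Among non-carriers the link between intake and arm may be weaker or absent.

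Suppose PLI lowers body fat for any reason, such as motivation. A model without the arm credits part of that effect to diet in carriers and not in non-carriers, and this difference is the genotype-by-diet term. Randomisation does not prevent it, because the regressor is a post-randomisation variable.

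At stake are the trial's gene-diet conclusions. An interaction could be reported where only a programme effect exists.

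**Working it through.** **1. Inputs from the article.** The Sample size calculation section gives a 4-point difference in body fat percentage, SD 6.1, 80% power, 5% alpha and 20% dropout. The Cohort randomization section gives 140 participants. The article gives no figure for the genotype-by-diet models. Its own sample size reproduces: n per arm = 2(1.96 + 0.84)² × 6.1² / 4² = 36.5, rounded up to 37, or 74 in total.

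**2. Assumptions, not in the article.** Carrier share is 20%, 40% or 50%. Advice shifts intake in PLI carriers by s = 0.5, 1 or 1.5 SD. Non-carriers do not shift unless stated. The programme effect is E = 4 or 2 points, the same in both genotypes and not acting through diet. There is no true diet effect, no true interaction and no clustering. The analysed number is 140, or 140 × 0.8 = 112 after dropout.

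**3. Expected false interaction without an arm term.** With 1:1 arms and within-arm intake SD 1, among carriers Cov(outcome, intake) = −E·s/4 and Var(intake) = 1 + s²/4. The slope among non-carriers is zero. The interaction coefficient is therefore

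b = −(E·s/4) / (1 + s²/4), in points per SD of intake.

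For E = 4:
- s = 0.5: −0.5/1.0625 = −0.47
- s = 1: −1/1.25 = −0.80
- s = 1.5: −1.5/1.5625 = −0.96

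Simulation (140 participants, 50% carriers) gave −0.47, −0.81 and −0.97, which agrees.

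**4. False-positive rate of the interaction test at nominal 5%, E = 4, no arm term.**

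| Intake shift | 112, 40% carriers | 140, 20% carriers | 140, 50% carriers |
|---|---|---|---|
| 0.5 SD | 6.5% | 6.1% | 7.9% |
| 1 SD | 10% | 9.9% | 11.7% |
| 1.5 SD | 14% | 12.9% | 17.3% |

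The 140-participant columns use 4,000 replicates. The Monte Carlo standard error of the largest entry is √(0.173 × 0.827/4000) = 0.6 percentage points.

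**5. Sensitivity.**
- With E = 2 the rates are 5.5%, 6.6% and 7.1% (112, 40% carriers) and 4.6% to 8.0% (140, 20% or 50% carriers).
- With no programme effect, or no genotype-driven shift, they are 4.3% to 5.5%.
- If non-carriers shift half as far in the same direction, the false coefficient shrinks. At E = 4 and s = 1 it is −0.80 − (−0.47) = −0.33, and the rate is about 5-6%. With equal shifts it is nominal. With opposite shifts the two slopes have opposite signs, so the bias is larger.

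**6. With study group added.** In every 140-participant scenario the rate returned to 4.3-5.7% and the mean coefficient to about zero. Adding arm × genotype as well gave 4.3-5.4%, so it was not needed here.

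**7. Number of open pairs.** Six genes linked in the Background to diet or weight approaches, times about eight dietary components in the Outcomes section, gives 48 pairs per outcome. If all were tested at 5% and were independent, the chance of at least one false positive would be 1 − 0.95⁴⁸ = 0.91. Counting 42 or 54 pairs gives 0.88 or 0.94.

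**The case against.** **The article is silent; it does not exclude the arm.** A reader might infer that the plan has chosen to pool the arms without adjustment. The text does not say so. Covariates, population and visit are often left to a statistical analysis plan, and none is shown. A baseline analysis would fit the sentence as written, and by the Run-in section no lifestyle advice had been given by then. The contrast with the TPB sentence is only suggestive, since study group is itself one of the interacting terms there. This stands, and it limits the point to what happens if the model is fitted as written to pooled follow-up data.

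**The named test is not implicated.** A reader might infer that the bias reaches the tertiary objective, or that any gene-diet pair may be tested. Neither is supported. ACE rs4343 with sodium and water intake on water weight is named in advance, with a direction for sodium. Sodium and water are not among the PLI recommendations listed, and nothing shown says that ACE genotype set such advice. Only further pairs are open. Crossing every listed gene with every component would also overcount, because five genes are linked in the Background to endurance or strength rather than diet.

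**The size depends on assumptions.** Both arms had the same dietitian, the same number of one-on-one sessions and an extra 1.5-hour session, so contact was largely matched and a 4-point effect acting wholly outside diet is a strong assumption. PLI non-carriers also received DNA-based advice, so their intake may differ by arm too. This stands: the article does not determine the size. It does not remove the mechanism, which needs only a programme effect and an intake shift that differs by genotype. The trial hypothesises the first, and its advice is designed to bring about the second.

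**Conclusion.** The concern holds in a limited form. The sentence specifies genotype and diet only, while the intervention ties diet to genotype in one arm. On pooled follow-up data, the interaction test for pairs such as FTO and protein can be biased.

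Under the 4-point effect and 0.5-1.5 SD carrier shift, the false-positive rate is about 6-14%, reaching 17% in the least favourable combination in the table. It is close to nominal with a small programme effect or with similar shifts in non-carriers. These figures illustrate the mechanism and do not predict what this trial will show.

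The pre-named ACE analysis is not shown to be affected. The primary and secondary comparisons between arms do not use this model. The point is still worth acting on, because one covariate removed the bias in simulation.

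**What to change.** - State the time point and population for the genotype-by-diet regressions, and include study group as a covariate. An arm main effect was enough in simulation, where the programme effect was the same in carriers and non-carriers.
- Alternatively, fit these models on baseline data, before any advice. They then describe habitual intake and not response to the programme.
- Keep ACE rs4343 with sodium and water intake, on water weight, as the tertiary test. Label all other gene-diet pairs exploratory.

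The cost is a few words and one model term. The downside is slightly less precise interaction estimates.

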#### Outcomes

The primary outcome in this study is change in percent body fat. Secondary outcome measures include changes in: dietary intake (calories, fat, protein, carbohydrates, unsaturated fat including mono- and poly-unsaturated fat, saturated fat, and sodium), physical activity, attitudes, subjective norms, behavioural control, intention to make lifestyle changes, weight and BMI.

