#### Sample size calculation

Seventy-four participants (*n* = 37 per group) are needed in this study to detect a clinically meaningful difference of 4% in body fat percentage, assuming 80% power, an alpha of 5%, and a standard deviation of 6.1% [43]. We aimed to recruit 88 participants (*n* = 44 per group) to account for the potential dropout rate of 20%. While minimal research exists outlining a clinically meaningful change in body fat percentage, a 5% change in weight (which would come from fat mass, water weight and/or muscle mass) is often reported to be clinically meaningful [44]. Furthermore, clinical experience from the registered dietitians involved in this study helped to determine the clinically meaningful 4% difference mentioned above. This difference has also been supported in published reference standards of body fat percentage in Caucasian adults which indicate that a 4% change in body fat percentage is associated with a 1 – 2 decile change on the reference standards charts [45].

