#### Cohort randomization

A cohort randomization model was used rather than subject randomization to allow all participants in a given GLB™ group to obtain the same intervention. At the time of randomization, 12 cohorts (GLB™ groups) were randomized 1:1 to either the personalized lifestyle intervention (PLI) based on genetics, or the standard lifestyle intervention (SLI) based on population-based guidelines. It was anticipated that 12 groups of approximately 7 participants each would be needed to obtain the desired sample size of 88 participants. Prior to obtaining informed consent from participants, randomly permuted blocks were generated using the original generator on an internet-based randomization program [46]. Since participant recruitment was quicker than anticipated and there was an even 1:1 split of a PLI and a SLI group in the last two randomized groups, only 10 of the randomized groups (5 PLI groups, 5 SLI groups) were used, resulting in a total of *N* = 140 participants in the study (mean number of study participants per group ± SD = 14.0 ± 4.1).

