#### Baseline data collection

All data are entered into the database using unique study codes for each participant and is securely stored in a locked cabinet, in a locked office. Baseline data consisted of a combination of in-person, online, and telephone data collection methods.

Trained research assistants collected 3-day food records over the phone using the validated multiple-pass method [47]. To reduce participant burden, each participant chose to have either 3 separate phone calls (one for each day of intake), or 1 phone call (for all three days of intake). One weekend day and two weekdays were collected. In rare cases where research assistants were unable to reach participants over the phone, the food records were collected in-person at the EEFHT. The food records were then analyzed using the Canadian Nutrient File within the nutritional analysis software program *ESHA Food Processor* (version 11.1).

Participants also completed a self-administered past-month, semi-quantitative, online food frequency questionnaire, the *Canadian Diet History Questionnaire II (CDHQII)*. This questionnaire is a modified version of the *United States Diet History Questionnaire* adapted for Canadian data [48]. Most participants completed this questionnaire away from the EEFHT, but in cases where participants did not have internet access at home (*n* = 3), the CDHQII was self-administered at the EEFHT.

In-person baseline data collection included: measured height and weight (used to calculate BMI), a BIA assessment to obtain body composition data (using the *Body Stat 1500MDD)*, a past-week physical activity recall (used to calculate metabolic equivalents), a baseline demographic questionnaire, a list of medications, and a TPB questionnaire. To optimize reliability, weight and height measurements were taken on the same *Health O Meter Professional* weigh scale and stadiometer, and body composition was assessed using the same BIA machine. The TPB questionnaire was developed based on Ajzen’s Guide to Constructing a TPB Questionnaire [49]. The results for weight, body fat percentage, body fat (kg), lean weight, and water weight from the BIA were communicated to participants during their in-person baseline data collection visit.

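### The primary contrast is a between-arm difference in change in percent body fat with no baseline term named; adding the baseline value already collected would be a free, modest gain

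*Protocol article*

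**What the plan says.** All references are to the protocol article.

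- **Outcomes:** "The primary outcome in this study is change in percent body fat".
- **Statistical analysis plan:** "Generalized linear mixed-effects models will be used to test between group differences from baseline to each follow-up period for each outcome indicator". No covariate is listed. The section does not call the analysis unadjusted and does not rule out a baseline term.
- **Baseline data collection:** "In-person baseline data collection included: measured height and weight (used to calculate BMI), a BIA assessment to obtain body composition data". Under Run-in, this visit falls before the intervention starts and no lifestyle advice is given in between.
- **Sample size calculation:** "Seventy-four participants (*n* = 37 per group) are needed in this study". The inputs behind that number are a 4-point difference, power of 80%, alpha of 5% and an SD of 6.1. The text does not say whether 6.1 is the SD of the level or of the change.
- **Cohort randomization:** "12 cohorts (GLB™ groups) were randomized 1:1". Ten groups were used, five per arm, with 140 participants and 14.0 ± 4.1 per group.
- **Discussion:** major confounders of behaviour change are said to be accounted for, but no variable and no method is given.

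**The concern.** The article fixes the contrast: the arms are compared on movement from baseline to each follow-up visit. If baseline is one of the repeated outcomes in the mixed model and each arm has its own baseline mean, the arm-by-visit contrast is the difference in mean change.

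That has two known costs relative to using baseline as a covariate:

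- It is less precise whenever the correlation between baseline and follow-up is below 1.
- It subtracts the whole baseline difference, although only a fraction r of that difference is expected to persist. If one arm happens to start higher, it is also expected to fall further without any effect of treatment.

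The second cost matters more here than in an individually randomised trial of the same size. Only ten groups were randomised, so any similarity within groups widens the chance difference between arms at baseline. The covariate that would deal with both costs has already been measured.

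**Working it through.** **The plan's own figure.** Two-sided alpha 5%, power 80%, SD 6.1, difference 4: n per arm = 2 × (6.1 × (1.960 + 0.842) / 4)² = 36.5, rounded up to 37, or 74 in total. The stated figure reproduces. It uses 6.1 directly and involves no baseline correlation.

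**Inputs.** From the article: SD 6.1; target difference 4 points; 140 participants in 10 groups of 14.0 ± 4.1. Assumed, because the article does not give them: r from 0.5 to 0.9; ICC of baseline body fat from 0.01 to 0.10; 70 participants per arm; equal SD at baseline and follow-up; 6.1 read as the between-person SD.

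**Precision.** With between-person SD σ:

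- change score: variance 2σ²(1−r)
- baseline-adjusted: variance σ²(1−r²)
- ratio adjusted/change: (1−r²) / [2(1−r)] = (1+r)/2

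| r | ratio | variance saved | n per arm if 6.1 is the SD of change |
|---|---|---|---|
| 0.5 | 0.75 | 25% | 28 instead of 37 |
| 0.7 | 0.85 | 15% | 32 |
| 0.8 | 0.90 | 10% | 33 |
| 0.9 | 0.95 | 5% | 35 |

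The last column is 36.5 × (1+r)/2, rounded up. These ratios concern participant-level variance only, not the between-group component.

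**Chance baseline difference D.** The coefficient of variation of group size is 4.1/14 = 0.293, so the effective group size is 14 × (1 + 0.293²) = 15.2. The design effect is DE = 1 + (15.2 − 1) × ICC, and SD(D) = 6.1 × √(2 × DE / 70).

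| ICC | DE | SD(D), points | chance that D exceeds 2 points either way |
|---|---|---|---|
| 0.01 | 1.14 | 1.10 | 7% |
| 0.05 | 1.71 | 1.35 | 14% |
| 0.10 | 2.42 | 1.60 | 21% |

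**What a change score leaves.** Given D, the error is about −(1−r) × D. For D of one SD, the size of the shift in points is:

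| r | ICC 0.01 | ICC 0.05 | ICC 0.10 |
|---|---|---|---|
| 0.7 | 0.33 | 0.40 | 0.48 |
| 0.8 | 0.22 | 0.27 | 0.32 |
| 0.9 | 0.11 | 0.13 | 0.16 |

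So the shift is 0.1 to 0.5 points, or about 3% to 12% of the 4-point target (0.11/4 and 0.48/4). At r = 0.5 it would be 0.55 to 0.80 points.

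**Sensitivity to the meaning of 6.1.** If 6.1 is the SD of change, the between-person SD is 6.1/√(2(1−r)). The shift is then √((1−r)/2) times the SD(D) values above: 0.43 to 0.62 points at r = 0.7 and 0.25 to 0.36 at r = 0.9. The order of magnitude is the same.

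**The case against.** The strongest objection is that nothing in the article says the comparison is unadjusted. The Outcomes section defines a variable; the analysis section names a model class and a contrast. Regressing change on arm plus baseline gives the same arm effect as regressing the follow-up value on arm plus baseline. A mixed model with a common baseline mean also fits the wording and is about as efficient. A covariate list is commonly left to a fuller document, which is not shown. This stands: a reader might infer that the trial will run an unadjusted analysis, but the article supports only that it names no baseline term. What remains is that the contrast as written, fitted in the ordinary way, is a change score, and that a better choice is available.

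Other strong readings also fail:

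- **That baseline imbalance stays in the estimate.** A change score removes the raw difference. Only (1−r) of it remains, with opposite sign, and across randomisations there is no systematic bias.
- **That true power is already below 80%.** This depends on an ICC the article does not give. With 140 analysed, SD 6.1 and a t-test on 8 degrees of freedom, power is about 89% at ICC 0.01, 74% at 0.05 and 59% at 0.10. The clustering question is separate.
- **That session choice made the arms differ.** Under Interventions, participants were blinded to assignment when they chose. Under Staggered cohorts, each arm had three day and two evening groups. One unblinded author did enrol and schedule participants, but baseline adjustment would not by itself cure a recruitment bias from that source.
- **That the arms are unbalanced by sex.** The article gives no sex distribution.

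**Conclusion.** The point holds as a recommendation of modest size. The article defines the primary comparison as a between-arm difference in change and names no use of the baseline value. Fitted with arm-specific baseline means, that comparison is valid over randomisations but less precise than it could be, and conditionally off by about −(1−r)D after a chance imbalance.

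How much this matters turns on r. If repeated body fat readings correlate at about 0.9, the gain is about 5% of participant-level variance and the 1-SD shift is 0.11 to 0.16 points, which is minor against 4. At 0.7 it is 15% and 0.33 to 0.48 points, which is worth having. Every size quoted rests on an assumed r and ICC, and the shifts also rest on reading 6.1 as the between-person SD. The stated sample size reproduces, and this point does not challenge it.

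**What to change.** State the baseline handling in the primary mixed model, in one of two forms:

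- model follow-up percent body fat on arm, visit and arm-by-visit, with baseline percent body fat and its interaction with visit as fixed covariates; or
- keep baseline as a repeated outcome and constrain the two arms to a common baseline mean.

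Either form goes alongside random effects for GLB group and participant. Handle weight, BMI and the other continuous outcomes the same way, each with its own baseline. Adjustment for sex is optional. If the intended model already does this, one sentence saying so is enough.

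The cost is a line in the analysis plan, ideally fixed before the allocation is unblinded to the statistician. No new data are needed, and a participant-level covariate uses almost none of the 8 between-group degrees of freedom (10 groups less 2 arms).
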